### Sample size and sampling procedures

The estimated sample size for this study is 6,390, based on the assumptions of a 28 percent death rate from a retrospective study, a design effect of 2.5, and a 20 percent loss to follow-up. A baseline evaluation or assessment will be performed immediately after screening. After baseline assessment, all patients will be followed-up daily until discharge according to WHO and National discharging guideline and followed as per schedule after discharged. Study subjects enrolled will be followed up for 12 months after enrollment for the specific objective related to virology and immunology, clinical course of the disease, response to treatment, effect of COVID-19 in pregnant mothers and birth-related effects of COVID-19. Enrolled cases will be followed up at 2 weeks, 3 months, 6 months, 9 months, and 12 months post-discharge. A visit window of ± 7 days may be applied to these visits. Patients discharged after recovery will be followed up according to the follow-up schedule.

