## Background

On March 11, 2020, the World Health Organization (WHO) declared Corona Virus Disease (COVID-19) to be a pandemic [1]. The current new emerging virus is a different strain of virus from SARS and MERS CORONA viruses. The difference is not only limited to genetic makeup but also in the clinical presentations, case fatality, and the rate of spread across the globe (surveillances). The swift spread of the virus is largely attributed to its stealth transmission, for which infected patients may be asymptomatic or exhibit only flu-like symptoms in the early stage. These undetected transmissions present a remarkable challenge for the containment of the virus and pose an appalling threat to public health [2]. COVID-19 has become one of the leading causes of mortality around the world.

As of August 03, 2021, there have been 200,508,148 confirmed cases and 4.26 million deaths reported worldwide and nationally 281,300 confirmed cases and 4,395 deaths reported [3]. To this end, the COVID-19 Global Research and Innovation Forum recommended each country and region to conduct research and generate evidence in their respective local context to strike the right balance between stopping transmission now and prepare for the future [4].

COVID-19 has also sparked fears of an impending economic crisis and recession [5]. Social distancing, self-isolation and quarantine, travel restrictions and border shut downs have led to a reduced workforce across all economic sectors and caused many jobs to be lost. Schools have been closed down, and the need for commodities and manufactured products has decreased [6]. Along with its high infectivity and fatality rates, there has been mass fear of COVID-19, termed as “coronaphobia”, that has generated a plethora of psychiatric manifestations across the different strata of the society [7]. The COVID-19 itself, multiplied by forced quarantine to combat the disease applied by nationwide lockdowns can produce acute panic, anxiety, obsessive behaviors, hoarding, paranoia, depression, and post-traumatic stress disorder (PTSD) [7, 8].

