## Methods/design

### Aim and study setting

In this multi-site cohort study, we aimed to determine the natural history of the disease; clinical features and management, epidemiological characteristics, immunological, virological courses and treatment response of the disease, effects of diets on the nutritional status on the disease progression, effect of the disease on pregnancy and birth outcomes, and the effect of traditional/modern treatment on COVID-19 outcomes among patients admitted to treatment centers in Ethiopia. Therefore, the study findings will generate scientific data for a systematic understanding of natural history, epidemiological characteristics, clinical features, and management of COVID-19 which will, in turn, enable the country’s health sector to develop strategies to prevent and control the pandemic before it poses further health and socioeconomic crises. The research question of this study is “Do different individual host factors and environmental situations influence clinical, epidemiological, and viral outcomes of COVID-19 infection?”.

The study will be conducted in all Federal treatment centers, including Ekakotebe, Yekatit-12, St. Peter Specialized hospitals, SPHMMC, Millennium hall center in Addis Ababa, and Regional Hospitals including Mekelle, Semera, Bahir Dar, Adama/Mojo, Hawassa, Jijiga, Harar, DireDawa, Metekel or Benishangul Gumuz, and Gambela dedicated to COVID 19 treatment.

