### Study population

This study will enroll individuals with confirmed infection with COVID-19 at selected Federal and Regional Hospitals irrespective of their differences (age, sex, symptoms, severity, and any other conditions). The patients' follow-up will be done strictly within the management adapted to their infection.

Individuals/patients in the study hospital or area will be eligible for inclusion if they meet the following criteria: (1) patient is admitted to selected treatment centers (Federal and Regional’s Hospitals) with COVID-19 confirmed by RT-PCR; and (2) consents to be enrolled in the follow-up study and provide all necessary information/data, blood sample, and nasopharyngeal swab for testing. Patients will be excluded if: (1) a subject deprived of freedom, subject under a legal protective measure; (2) refusal by a participant, parent or appropriate guardian or representative; (3) not willing to stay 12 months in the cohort in Ethiopia; (4) is already involved in the COVID-19 clinical trial or other interventional studies; (5) not capable of understanding or complying with the study protocol or provide consent; (6) anticipated transfer to another hospital that is not a study site within 72 h.

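### The sample size rests on a 28% death rate that the article's own population and national figures make implausible, so the models of determinants of death will probably have far fewer deaths than 6,390 patients suggest

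*Protocol article*

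**What the plan says.** Under Sample size and sampling procedures, the article states: "The estimated sample size for this study is 6,390, based on the assumptions of a 28 percent death rate from a retrospective study", together with "a design effect of 2.5, and a 20 percent loss to follow-up". It does not describe the retrospective study or say why its death rate suits this cohort.

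Under Study population, patients must be admitted to a selected treatment centre with RT-PCR confirmation, and are enrolled "irrespective of their differences (age, sex, symptoms, severity, and any other conditions". The Methods paragraph of the abstract also says that symptoms do not matter for enrolment. Data collection provides for asymptomatic cases followed at home. Background reports "nationally 281,300 confirmed cases and 4,395 deaths reported" as of 3 August 2021.

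Death is part of a primary outcome in both the abstract and the outcomes section. Under Data processing and statistical analysis, predictors that appear as risk factors in bivariate analysis go into the multivariable model, and a random subsample is held back for validation.

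**The concern.** A 28% death rate would suit a severely ill hospital series. This cohort is defined without regard to severity, and the only Ethiopian mortality figure in the article is about one eighteenth of the planning value. The two figures describe different populations, but the article does nothing to bridge them.

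What is at stake is the information in the models of determinants of death. These depend on the number of deaths, not the number of patients. A reader who sees 6,390 patients and 28% will assume well over a thousand deaths and accept a large multivariable model. If mortality is a few percent, the same model would be fitted to a small fraction of that, with predictors chosen by bivariate screening and part of the data set aside for validation.

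**Working it through.** **Inputs.** N = 6,390, p = 0.28, design effect 2.5 and loss 20% (Sample size and sampling procedures); 4,395 deaths and 281,300 cases (Background). The article gives no margin or confidence level for the sample size.

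**The plan's own figure.** The single-proportion formula is n = z²p(1−p)/d². At 99% confidence with z written as 2.57 and d = 2.5 points:

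- 2.57² × 0.28 × 0.72 / 0.025² = 2,130
- 2,130 × 2.5 = 5,325
- 5,325 × 1.2 = 6,390

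With z = 2.576 the result is 6,420. At 95% and ±2 points it is 5,808 (loss as ×1.2) or 6,050 (loss as ÷0.8). So one round margin yields the stated figure exactly. This does not prove that it was the margin used.

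**National reference.** 4,395 / 281,300 = 1.56%, and 28 / 1.56 is about 18.

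**What 28% would mean.**

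- Expected deaths: 0.28 × 6,390 = 1,789. As a share of reported national deaths, 1,789 / 4,395 = 41%. The cohort's size is 6,390 / 281,300 = 2.3% of national cases. This is a comparison of scale; the cohort and the national count do not cover the same period.
- If every reported national death had occurred in an admitted patient, 28% mortality among admissions would require only 4,395 / 0.28 = 15,696 admissions, or 5.6% of confirmed cases. That is hard to square with centres whose enrolled patients include asymptomatic cases.
- Two features of the design tend, if anything, to remove high-risk patients. Those unable to understand, comply or consent are excluded, and screening takes place one to two days after admission, so the earliest deaths may be missed.

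**What lower mortality does.** Patients after loss: 6,390 × 0.8 = 5,112. Absolute 95% half-width: 1.96 × √(p(1−p) × 2.5 / 5,112). Relative half-width: that value divided by p. The 5% and 10% rows are assumed values, because the article gives no mortality for admitted patients.

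| Mortality | Deaths in 6,390 | Deaths in 5,112 | Absolute half-width (points) | Relative half-width |
|---|---|---|---|---|
| 28% | 1,789 | 1,431 | ±1.95 | ±7% |
| 10% | 639 | 511 | ±1.30 | ±13% |
| 5% | 320 | 256 | ±0.94 | ±19% |
| 1.56% | 100 | 80 | ±0.54 | ±34% |

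At 10%, more than six times the national figure, 511 / 1,431 = 36% of the implied deaths would be available. At 5% it is 256 / 1,431 = 18%.

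**The case against.** The strongest objection is that the comparison is not like for like. The national figure covers all confirmed cases, while the cohort is restricted to admitted patients followed for 12 months, and both features raise mortality. This stands: 1.56% cannot be read as a forecast, and the cohort's rate should exceed it. It does not make 28% plausible for an all-severity cohort, and the article offers no other support. The national count is also dated August 2021, after registration and the stated start, so it may not have been available when the study was sized. That explains the choice of 28% but does not justify it for this population.

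Second, if 6,390 came from a precision formula, overstating mortality is harmless for estimating the death rate. This stands too. Holding ±1.95 points at 1.56% would need only about 486 patients under the same design effect and loss. The article states no target number of deaths, and the other primary outcomes, recovery time and viral shedding, do not depend on deaths.

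Third, the deaths after loss are somewhat pessimistic, because patients are followed daily until discharge and in-hospital deaths would be seen before most loss occurs. The true count at each rate lies between the two deaths columns, which does not change the picture. The analysis section also names rare events among the conditions to be assessed. That is a useful start, but it does not tie model size to deaths.

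A reader might also infer two stronger criticisms, and neither is supported. One is that 6,390 does not follow from any round margin; the calculation at 99% and ±2.5 points shows otherwise, and the unstated margin may be in the full protocol. The other is that "a design effect of 2.5" is too small for the number of centres. That argument needs assumed intracluster correlations and 15 centres of equal size, and nothing in the article contradicts 2.5.

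**Conclusion.** The planning rate is implausible for the population described, and the article gives no reason for it. The harm is confined to relative precision of the death rate and to the models of determinants of death. Over 10% to 1.56% mortality, deaths after loss fall from the implied 1,431 to between 511 and 80, and the relative half-width grows from ±7% to between ±13% and ±34%. Absolute precision improves throughout. The conclusion rests on the stated design effect and loss, and on inpatient mortality being well below 28%. The article makes that likely but does not establish it. It would go too far to say that the cohort will see 1.56% mortality, or that 6,390 is too small for the study as a whole. This should be fixed before analysis, but it is not a fault that stops the study.

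**What to change.** Keep 6,390. In the sample size paragraph, retain the statement that 28% was the planning value, because it is the real basis of the figure, and add that it probably overstates mortality in a cohort of all severities. Give expected deaths with absolute and relative precision over a range such as 1.6% to 28%, as in the table above.

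In the analysis section, replace entry of every predictor significant in bivariate analysis into the death model with a model whose number of parameters is limited by the deaths observed. Use penalised regression, for example Firth's method, if deaths are few.

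The cost is a rewritten paragraph and one changed modelling rule, with no additional patients. The downside is that the stated support for the mortality models becomes less favourable.

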### Primary outcome and secondary outcomes

The primary outcome variables are treatment outcome (active cases, recovered, death or transferred for further treatment), recovery time, and duration of viral shedding (the time from the first positive RT-PCR results to the occurrence of the last positive RT-PCR results or negative RT-PCR results). The secondary outcomes include clinical symptoms and signs (major); co-morbidities; status at last follow-up (survival, severity, virus detection); laboratory biomarkers; duration of symptomatic phase, inpatient stay, ICU stay; viral loads; anti-SARS-CoV-2 antibody titer; imaging with results; therapeutic measures; plasma 25-hydroxyvitamin D concentrations; dietary history; micronutrient status (zinc and vitamin A); fasting blood sugar; weight, height, BMI; total cholesterol (TC), triglycerides (TG), HDL-C, LDL-C and body composition(waist circumference); genetic frequency shifts (genotypic variations); obstetric and gynecologic history; pregnancy status/test; clinical status; supplemental oxygen; non-invasive ventilation or oxygen delivery devices/ respiratory support. We will also collect confounding variables include socio-demographic variables (age, sex, education status); status cases at the time of enrollment; and months after the first positive test.

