**Methods:**

A multi-center cohort study design will be performed. Patients with confirmed COVID-19 infection admitted to selected treatment centers will be enrolled irrespective of their symptoms and followed-up for 12 months. Baseline epidemiological, clinical, laboratory and imaging data will be collected from treatment records, interviews, physical measurements, and biological samples. Follow-up data collection involves treatment and prognostic outcomes to be measured using different biomarkers and clinical parameters. Data collection will be done electronically using the Open Data Kit (ODK) software package and then exported to STATA/SPSS for analysis. Both descriptive and multivariable analyses will be performed to assess the independent determinants of the treatment outcome and prognosis to generate relevant information for informed prevention and case management. The primary outcomes of this study are death/survival and viral shedding. Secondary outcomes include epidemiological characteristics, clinical features, genetic frequency shifts (genotypic variations), and nutritional status.

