### Data collection

Data collection will be done electronically using the REDCap software package and data documentation will be performed from a retrospective history of the patient and prospectively after treatment is finalized. Contact information such as home address and telephone number will be collected to facilitate follow up and for tracking defaulters of follow-up. For asymptomatic cases whose follow-up is undertaken at home, their home address, GPS coordinates and geospatial data for all participants will also be registered by trained data collectors (study nurse or doctor). Data will be gathered from patients and follow up cases through interviews by physicians/nurses at each treatment center using a questionnaire and standardized Case report form (CRF). Biological samples will also be collected at baseline and follow up when samples are taken in the context of care to meet the research objectives. Five-milliliter venous blood will be collected using a serum separator tube and 4 mL venous blood will be collected using a test tube containing anticoagulant. Viral load measures in a body fluid using Abbot and Rosh reagents and platforms will be measured. Phylogenetic analysis of SARS-CoV-2: genotyping of different types of SARS-CoV-2 from Ethiopian isolates under different settings will be done using a next-generation sequencer at Ethiopian Public Health Institute (EPHI). Imaging: chest x-ray, ultrasound scan, chest computed tomographic (CT) scans data will be retrieved if available. Laboratory tests for D-dimers, platelet count, PT, PTT, INR, D- Dimer, and serum ferritin will be measured.

The screening will be performed within the period between one to two days of admission to the hospital to review study inclusion/exclusion criteria; obtain prior medical and concomitant medication histories; perform a complete physical examination, including height, body weight, and vital signs (blood pressure, BP, heart rate, HR), Oxygen saturation (SpO2) with pulse oximetry; and collect a blood sample for laboratory testing on screening day.

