### Data processing and statistical analysis

Data collection will be done electronically using the ODK software package and then exported to STATA/SPSS for data cleaning, management, and statistical analysis. The data will be cleaned and checked for outliers, all assumptions, and analyzed using appropriate statistical software (STATA, Python, and/or R statistic software).The analysis will be performed by trained personnel (epidemiologists, statisticians, health economists) using the appropriate statistical methods. Statistical analyses strategy will be based on specific study objectives and the nature of the outcome variables, the various assumptions to be assessed and associated scenarios to be considered, and the criteria to be used for decision-making at each stage including management of incomplete data, model building procedures, and evaluating the validity of models and the robustness of results. Data will be assessed for consistency, missing values, presence of outliers and implausible values, and different statistical assumptions including univariate and multivariate normality of distributions, the linearity of hypothesized relationships, the proportionality of hazard, and the presence of rare events among others.

A descriptive summary of the continuous variables will be reported as mean (± SD) and median (IQR), and categorical variables will be summarized as counts and percentages. A correlation or chi-square test will be performed for appropriate variables.

Predictors that have been identified as risk factors in the bivariate analysis will be entered into multivariable analysis to isolate independent determinants of the outcome. Multiple linear and generalized linear regression models will be fitted depending on the type of outcome variable. Cox-proportional hazard ratio (HR) will be used for time-to-event variables including the time to recovery, and other time to event variables. Time to event analysis, semi and parametric survival analysis will be conducted as appropriate.

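### Viral shedding is timed from the first positive RT-PCR, and no listed confounder measures how far into the infection that test fell, so differences in testing delay can appear as differences in clearance

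*Protocol article*

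**What the plan says.** The Abstract (Methods) of the protocol article states: "The primary outcomes of this study are death/survival and viral shedding". The section on primary and secondary outcomes defines the second of these as "duration of viral shedding (the time from the first positive RT-PCR results" and continues "to the occurrence of the last positive RT-PCR results or negative RT-PCR results". The time origin of a primary outcome is therefore fixed.

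Under Study population, confirmed cases admitted to the study centres are enrolled "irrespective of their differences (age, sex, symptoms, severity, and any other conditions". The Data collection section begins one provision with "For asymptomatic cases whose follow-up is undertaken at home", so asymptomatic cases are expected. No entry criterion limits the time from infection or symptom onset to the first positive test.

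The outcomes section lists the confounders to be collected: age, sex, education, status at enrolment, and "months after the first positive test". The secondary outcomes include "duration of symptomatic phase, inpatient stay, ICU stay", so a symptom-onset date is implied, but the article does not use it as an origin or as an adjustment.

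The stated research question is whether host and environmental factors influence clinical, epidemiological and viral outcomes. For the analysis, "Cox-proportional hazard ratio (HR) will be used for time-to-event variables".

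**The concern.** The first positive test marks when a case was found. It does not mark when shedding began. An asymptomatic patient cannot have been tested because of their own symptoms, so the routes to testing must differ within this cohort, and the stage of infection at the first positive test may well differ with them. A patient tested late has already used up part of the shedding period before the clock starts.

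This matters little for describing duration after diagnosis. It matters when groups are compared by hazard ratio, which is how the research question would be answered. Part of a hazard ratio for viral clearance could then reflect access to testing or the reason for it. The listed time variable does not help: months after the first positive test runs forward from the same origin and carries no information about the time before it.

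Two other safeguards in the analysis section do not reach the problem. The Benjamini–Hochberg adjustment addresses chance findings, not bias. The held-back random subsample has the same time origin, so it would reproduce the same spurious association.

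**Working it through.** The plan gives no figure for shedding duration or testing delay, so there is nothing to reproduce on this point. The sample size of 6,390 rests on a death rate. It is used here only to choose a simulation size: 6,390 × 0.8 / 2.5 = 2,044.8, or about 2,045 after removing the 20% loss and the design effect of 2.5.

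**Identity.** Let T be the time from the start of infection (or of detectable shedding) to clearance, D the delay to the first positive test, and S the duration as defined. Then S = T − D for patients still positive when tested (D < T). If T has the same distribution in two groups and mean D differs, mean S differs by about the same amount in the opposite direction. With mean T = 24 days and mean delays of 5 and 9 days, mean S is about 24 − 5 = 19 against 24 − 9 = 15 days, although clearance is identical.

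**Simulated hazard ratios.** A Cox model on S compares the later-tested with the earlier-tested group. There is no true difference, so the correct value is 1. All distributions and delays are assumptions.

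| Assumed time to clearance (days) | Delay SD | Mean delays (days) | Hazard ratio |
|---|---|---|---|
| Gamma, mean 24, SD 7 | 2 | 5 vs 5 | 0.99 |
| same | 2 | 5 vs 7 | 1.27 |
| same | 2 | 5 vs 9 | 1.59 |
| same | 2 | 5 vs 11 | 1.98 |
| Mean 24, SD 12 | 2 | 5 vs 7 / 9 / 11 | 1.14 / 1.22 / 1.40 |
| Mean 24, SD 16 | 4 | 5 vs 7 / 9 | 1.05 / 1.13 |
| Lognormal, mean 15, 20 or 25, SD 40% of mean | 2.5 | 5 vs 5 | 0.99 to 1.01 |
| same | 2.5 | 5 vs 7 | 1.20 to 1.26 |
| same | 2.5 | 4 vs 8 | 1.35 to 1.55 |
| same | 2.5 | 3 vs 9 | 1.57 to 1.88 |

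The gamma and mean-24 rows use n = 2,045 (60 data sets for SD 7, 12 for the wider spreads). The lognormal rows use 500 per group and 12 data sets. Equal delays return a hazard ratio of about 1, so the spurious effect comes from the difference in delay. With SD 7, a gap of only one day gives 1.09. In the first block the median observed durations are 18.4 days against 16.4, 14.4 and 12.6 days for the unequal delays, and every such data set is significant. That last result reflects the narrow assumed spread.

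**Does adjustment work?** In the first block, adding D to the model gives hazard ratios of 0.99 to 1.01. So does running time from infection with delayed entry at the first positive test. Both use the true delay, which a real study does not observe.

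**Does status at enrolment already deal with it?** Only for the part of the delay that it explains.
- If a factor relates to delay solely through severity (20% against 40% severe, mean delays 5 and 9 days), the hazard ratio is 1.09 unadjusted and 1.00 after adjusting for severity.
- If the factor itself adds two days of delay and severity adds three, adjusting for severity leaves 1.24 to 1.26.

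**The case against.** The strongest case for the plan has four parts.

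1. **The origin is defensible.** The first positive RT-PCR is dated, objective and available for every patient. Symptom onset is recalled, and asymptomatic patients have none. This stands, and it is why the origin should be kept for description.

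2. **The documents do not describe how cases are found or how long testing takes.** A reader might infer that severe, rural or less educated patients are tested late and will appear to clear the virus faster. Nothing in the article supports that direction; severe illness could equally prompt earlier testing and reverse the sign. A reader might also take the values from 1.27 to 1.98 as the expected bias. They depend on a narrow assumed spread of clearance times, and wider spreads give about 1.05 to 1.40 for the gaps tried. This objection stands in full.

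3. **Some of the pathway is already covered.** Education and status at enrolment are listed, and status may capture severity, although it is not defined. Baseline work includes recording earlier test results and symptoms from before the study, and viral load is measured. This stands in part: the listed variables remove only the delay they explain, and the article does not tie the other data to the shedding analysis.

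4. **An article leaves the covariates of each model to the full plan, and this one promises to check models for omitted variables.** It is true that the absence of a detailed shedding model is no fault. But the article itself fixes the origin and names the confounders, and that list has no measure of time before the first positive test.

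**Conclusion.** The point holds in a limited form. As written, the definition of a primary outcome combined with the stated confounders leaves hazard ratios for clearance open to a time-origin bias. It affects factors associated with testing delay beyond what status at enrolment and education explain. It does not follow that every host factor will be biased, or that sicker patients will seem to clear faster.

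Size and direction cannot be determined from the documents. Under assumed gaps of 2 to 6 days in mean delay, the spurious hazard ratio for the later-tested group runs from about 1.05 to 2.0. It is larger with wider gaps and smaller when clearance times vary more. These figures assume identical true clearance and exactly known clearance times.

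This is a cheap improvement to a usable definition. It does not show that the outcome is invalid.

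**What to change.** - Keep the first positive RT-PCR as the origin for describing shedding duration.
- Record the date of symptom onset, which the symptomatic-phase outcome already implies, and add one item to the case report form: the reason for the first test (symptoms, contact, travel or screening). Collect both at enrolment, when recall is best.
- In symptomatic patients, include days from onset to first positive test and the reason for testing in the shedding models. A test taken before symptoms began gives a negative interval and should be kept as such.
- As a sensitivity analysis in the same patients, measure time from onset to clearance with delayed entry at the first positive test.
- Analyse asymptomatic patients as a separate stratum, by reason for testing.

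The cost is one form item, two model terms, one sensitivity analysis and a separate stratum. Onset dates carry recall error, and onset only approximates the time of infection, so the correction will be incomplete and should be reported as such.

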### Follow-up visits

Data collection at follow-up at 2 weeks, 3 months, 6 months, 9 months and 12 months was the same as at baseline and used to ascertain primary and secondary outcomes. The following tasks will be performed at these visits:Perform symptom-Directed physical exam,Obtain body weight and vital signs including pulse, respiratory rate and blood pleasure, oxygen saturation,Perform pulmonary function test (PFT),Record any symptoms,Spirometry to determine pulmonary function tests such as forced expiratory volume in the first second (FEV1), forced vital capacity (FVC) and FEV1/FVC ratio,Collect blood for serum chemistries including creatinine, electrolytes, total bilirubin, albumin, ALT, AST, total protein, CK, calculate CrCl, Ab tests,Collect mouth/nasal swabs for PCR tests,Collect urine for analysis, including pregnancy test (in women),Collect serum on-site as the back-up storage (3 mL serum) andCollect dietary history.

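### BMI and waist circumference are the body-size outcomes for a cohort of all ages that follows pregnant women, and the follow-up task list drops height and waist despite being described as equal to baseline

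*Protocol article*

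**What the plan says.** All references are to the protocol article.

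- **Outcomes.** The section on primary and secondary outcomes gives the body-size items as "weight, height, BMI; total cholesterol (TC), triglycerides (TG), HDL-C, LDL-C and body composition(waist circumference". Waist circumference is the only item offered as body composition. The same list also carries nutrition through "plasma 25-hydroxyvitamin D concentrations; dietary history; micronutrient status (zinc and vitamin A".
- **Role of nutrition.** The abstract's methods state: "Secondary outcomes include epidemiological characteristics, clinical features, genetic frequency shifts (genotypic variations), and nutritional status". The aim section includes diet and nutritional status in relation to disease progression, and the Background presents high BMI as a severity factor at every age.
- **Who is enrolled.** Study population takes confirmed cases "irrespective of their differences (age, sex, symptoms, severity, and any other conditions". It foresees minors, because one exclusion is "refusal by a participant, parent or appropriate guardian or representative". Another exclusion, "not capable of understanding or complying with the study protocol or provide consent", may limit the number of young children.
- **Pregnancy.** The sample size section names, among the objectives with 12 months of follow-up, "effect of COVID-19 in pregnant mothers and birth-related effects of COVID-19".
- **Measurements.** Baseline assessment lists height, weight and waist circumference. Follow-up visits first says that data collection equals that at baseline. Its task list then reads "Obtain body weight and vital signs including pulse, respiratory rate and blood pleasure, oxygen saturation", with no height and no waist.

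**The concern.** The article names one set of body-size measures for everyone, and two groups in the cohort do not fit it.

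In children, BMI changes with age during normal growth, so the same value means different things at different ages. In pregnancy, weight, BMI and waist rise with gestation and fall at delivery, which can happen within the 12 months of follow-up. The article names neither an age-standardised form nor a pre-pregnancy weight. An analysis of BMI against severity or death that pools these groups with other adults would mix body size with age and gestation.

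The second part is a data-collection problem. A height or waist that was not measured at a visit cannot be recovered later. If sites work from the follow-up task list, any follow-up BMI in a growing child must use an old height, and follow-up waist will not exist.

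**Working it through.** The plan states no figure on this point, so there is none to reproduce. The check compares the sections and then sizes the individual errors under assumed values.

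**1. Baseline list against follow-up list**

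| Item | Baseline assessment | Follow-up task list |
|---|---|---|
| Weight | yes | yes |
| Height | yes | no |
| Waist circumference | yes | no |
| Pregnancy test (women) | yes | yes |

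The sentence that opens Follow-up visits says the two are the same. For height and waist they are not, so a site cannot tell which to follow.

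**2. Outdated height in a growing child**

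BMI = weight (kg) / height (m)². If current weight is divided by baseline height squared, BMI is overstated by the factor (current height / baseline height)².

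- Assumed 6-year-old: 116 cm at baseline; 122 cm and 23 kg at 12 months.
- Current height: 23 / 1.22² = 15.5.
- Baseline height reused: 23 / 1.16² = 17.1.
- Ratio: (122/116)² = 1.106, so about 11% too high.
- Range, for an assumed child of 110 cm growing 4, 6 or 8 cm: (114/110)², (116/110)² and (118/110)² give +7.4%, +11.2% and +15.1%.

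A BMI-for-age z-score at follow-up would carry the same error, because it is built on the same BMI.

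**3. Gestational weight in BMI**

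- Assumed woman of 1.58 m and 60 kg: 60 / 1.58² = 24.0. With an assumed gain of 8 to 12 kg, 68 / 1.58² = 27.2 and 72 / 1.58² = 28.8.
- Assumed woman of 1.58 m and 55 kg: 22.0. With gains of 5, 10 and 15 kg: 24.0, 26.0 and 28.0.

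These shifts of 2 to 6 BMI units are due to the pregnancy alone and reverse largely at delivery.

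**4. How many participants this touches**

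The article gives no expected share of minors or pregnant women for this cohort. The Background puts children at 1–5% of cases worldwide. Applied to 6,390, that would be 64 to 320 (0.01 × 6,390 and 0.05 × 6,390). This is a scale only: the cohort consists of patients admitted in Ethiopia, and the capacity-to-consent exclusion may lower the number. For pregnant women there is no figure to scale from.

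**The case against.** The strongest reply is that the outcomes section is a list of variables, not an analysis rule, and that a condensed article may leave derivations to the full protocol or SAP. Age, sex, height and weight at baseline are enough to derive baseline BMI-for-age. Pregnancy status, obstetric history and repeated pregnancy tests allow pregnant women to be separated. The analysis section ties methods to the objectives and the type of outcome, and nowhere says that children, pregnant women and other adults are pooled in one BMI model. Nutrition also rests on vitamin D, zinc, vitamin A and dietary history. All of this stands, and it limits the point.

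A reader might go further and infer that healthy children will be counted as underweight and bias the mortality results. The documents do not support that, because they state no BMI cut-off and no underweight category. One can construct a figure. Assume a cut-off of 18.5, all minors of school age with mean BMI 15.5 (SD 1.5 to 2), 10% of adults underweight, and child mortality of 0.5%. The crude death risk ratio for underweight is then about 0.92 with 1% children and about 0.67 to 0.71 with 5%, when the true adult ratio is 1. Every input is assumed, and the result depends on the age mix. With older adolescents instead (mean 20, SD 2.5), about 27% fall below 18.5 and the ratio at a 5% share is about 0.91 to 0.92. It is also a crude ratio, whereas age is a named confounder and multivariable models are planned. It should not be quoted as the size of the problem.

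The reply does not reach the follow-up measurements. The sentence equating follow-up with baseline may mean that height and waist are intended, but the task list says otherwise. No analysis plan can supply a height or waist that was not taken. Nor is any pre-pregnancy weight named, so excluding pregnant women avoids the distortion without recovering their nutritional status.

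**Conclusion.** The point holds in a limited form. The article names BMI and waist as the body-size outcomes for a population in which they are not interchangeable across children, pregnant women and other adults. Its follow-up section is also inconsistent on whether height and waist are measured again.

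If the task list is followed, follow-up waist is missing for everyone. Follow-up BMI in a 6-year-old is about 11% too high at 12 months (7% to 15% across the assumed growth range). Gestational gain shifts BMI by about 2 to 6 units under the assumed weights.

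Misclassification is a risk and not a certainty, because no categories are stated. Its effect on the cohort's results cannot be computed without the shares of minors and pregnant women. Baseline BMI results within non-pregnant adults, and the primary outcomes themselves, are not affected.

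**What to change.** 1. Reconcile Follow-up visits with Baseline assessment by adding height (at least for minors) and waist circumference to the follow-up task list.
2. In the outcomes section, define body size by group: age- and sex-standardised BMI (BMI-for-age z-scores) for minors, and BMI and waist for non-pregnant adults.
3. Fit the models of BMI against severity and against death in non-pregnant adults, and report minors separately.
4. Leave pregnant or recently delivered women out of BMI and waist analyses unless pre-pregnancy weight is recorded. If it is to be used, add it to the baseline form.

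The cost is one short set of measurements at visits already scheduled, some wording, and a slightly smaller analysis set for the adult BMI models. The measurement part should be settled before follow-up data are collected, because missed heights and waists cannot be filled in afterwards.
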